| 4.6.3.3 Sensitivity analyses (incident eGFR <30ml/min/1.73m  ) | As healthcare services have been impacted heavily by the pandemic, there may not have been sufficient routine testing of patients to be able to detect a reduction in eGFR. As patients who are highest risk may be prioritised, we will also investigate for incident eGFR <30ml/min/1.73m  ... | We did not investigate for incident eGFR <30ml/min/1.73m  . | We identified an important effect on 50% reduction in eGFR and so this additional sensitivity analysis was not required.               |
| 4.6.3.4 Sensitivity analyses (eGFR equation)                               | We will assess how many individuals change CKD stage from the original CKD-EPI equation after switching to the 2021 equation. If there are marked differences in the number of people with CKD and within each CKD stage, we will undertake a                                                                | We did not undertake an analysis using the 2021 CKD-EPI eGFR equation.  | This equation has not yet been validated for use in clinical practice in the UK.                                                       |

|                                        |                                                                                                                                                                                                                                              |                                                                                                                                          |                                                                                                                                               |
|----------------------------------------|----------------------------------------------------------------------------------------------------------------------------------------------------------------------------------------------------------------------------------------------|------------------------------------------------------------------------------------------------------------------------------------------|-----------------------------------------------------------------------------------------------------------------------------------------------|
|                                        | sensitivity analysis using the 2021 equation instead for eGFR.                                                                                                                                                                               |                                                                                                                                          |                                                                                                                                               |
| 4.6.3.5 Sensitivity analyses (Age)     | As our main analyses will adjust for age in broad age bands, to ensure that we have fully accounted for age as a potential confounder, we will repeat analyses with age as the underlying timescale (allowing us to finely account for age). | We did not undertake this sensitivity analysis.                                                                                          | Our main analysis implicitly adjusted for exact age as our models were stratified by matched set (with age as one of the matching variables). |
| 4.6.3.7 Sensitivity analyses (Smoking) | In our main analyses we will assume that individuals with missing smoking status were non-smokers. To test this assumption, we will repeat our analyses restricting to those with known smoking status.                                      | In our main analyses, we undertook complete case analysis without making assumptions about individuals with missing smoking status data. | We decided to perform complete case analysis (i.e. the planned sensitivity analysis) to minimize effects of misclassification.                |
| 4.6.3.8 Sensitivity analyses (BMI)     | In our main analyses we will assume that individuals with missing BMI data have normal BMI. To test this assumption, we will repeat our analyses restricting to those with known BMI.                                                        | In our main analyses, we undertook complete case analysis without making assumptions about individuals with missing BMI status data.     | We decided to perform complete case analysis (i.e. the planned sensitivity analysis) to minimize effects of misclassification.                |

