### 2.1 COVID-19 and AKI

AKI describes a clinical state of potentially reversible reduction in kidney function. It is diagnosed when there is a  $\geq 50\%$  or  $\geq 26.5 \mu\text{mol/L}$  rise in serum creatinine (a biomarker of kidney function) on blood tests compared to baseline, or a reduction in urine output to  $< 0.5 \text{ ml/kg/hour}$  based on body weight. AKI is not unusual in acute illness (due to hypoperfusion and/or inflammatory processes), especially on a background of comorbidity (e.g., diabetes, CKD, heart failure), and factors including increasing age and socioeconomic deprivation also contribute.

Initial reports on the incidence of AKI in COVID-19 from China were low, and this may be because patients had fewer comorbidities and were admitted for less severe COVID-19 than in other settings. A more recent analysis of over 40,000 individuals in the International Severe Acute Respiratory and emerging Infections Consortium World Health Organization Clinical Characterization Protocol UK (ISARIC-WHO CCP-UK) study, a large prospective cohort comprising patients admitted with COVID-19 to over 250 hospitals across the UK up to early December 2020, found that 31.5% of patients developed AKI. As pre-admission serum creatinine data was unavailable, AKI could only be determined in patients who had at least 2 inpatient measurements and so it is possible people more likely to develop AKI were more likely to have repeated tests; conversely, patients with stable

elevated serum creatinine from the time off admission may have been misclassified as not having AKI resulting in underestimation. This study also found that 3% of over 80,000 inpatients required kidney replacement therapy (KRT), the treatment for severe AKI. Pre-existing CKD was strongly associated both AKI and KRT, as were physiological markers of more severe COVID-19 at hospital admission (i.e. tachypnoea and hypoxia). The variability in estimates of the incidence of AKI may reflect differences in national and local criteria for hospital admission as the risk of AKI in mild COVID-19 or asymptomatic SARS-CoV-2 infection remains unknown.

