#### **4.4.4 Follow-up start**

By using index dates 28 days after first recording of SARS-CoV-2 infection (i.e., date of testing in SGSS, date of primary care coding, or date of admission on SUS), we will be able to look back and further stratify the exposure by measures of SARS-CoV-2 severity (i.e. community, hospitalisation, critical care admission etc.).

For analyses comparing people after SARS-CoV-2 infection to a historical comparator group from 2018-2019, the matched historical comparators will be followed-up from exactly two years before the index date.

For analyses comparing people hospitalised for COVID-19 with an unmatched historical group of individuals hospitalised for pneumonia from 2018-2019, we will follow all eligible individuals from 28 days after their admission date for pneumonia.

For analyses comparing people after SARS-CoV-2 infection to a matched contemporary comparator group, we will follow all eligible individuals from the index date.

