#### **4.4.5 Follow-up end**

In all analyses we will follow individuals until the earliest of: record of specific kidney outcome under investigation, ESRD, death, no longer registered with GP practice, or study end. Individuals from the matched contemporary comparator group will also be censored at the date of first recorded SARS-CoV-2 infection and will transfer to the exposed group if they survive 28 days after this date.

For analyses using matched historical 2018-2019 comparators, the study end for people with COVID-19 will be the last available date for data at the time of extraction, and for

their matched comparators it will be January 31 2020 at the latest. Our choice of end of follow-up for people with COVID-19 is to be consistent with the available follow-up time for people in the historical comparator group, as we will no longer be able to follow people in the historical comparator group after February 2020 (as we will no longer be sure that those in our comparator group did not have COVID-19 after the start of the initial UK COVID-19 outbreak in February 2020). By allowing the same duration of potentially available follow up for people with and without COVID we will be able to ensure our results are not biased by allowing additional follow up for people with COVID-19 (and consequently allowing more time for them to develop the outcomes under investigation) compared to those without. By allowing the same duration of potentially available follow up for people with and without SARS-CoV-2 infection, we will be able to ensure our results are not biased by allowing additional follow up for people pre-pandemic.

For analyses with the contemporary comparator group, the study end will be the latest available date of fully linked data available on the day the initial cohort is extracted.

[figure not shown]

[figure not shown]

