*Figure 1* Graphical illustrations of potential study scenarios. **A-C: Examples of individuals with recorded SARS-CoV-2 infection.** A was followed-up from 28 days after SARS-CoV-2 infection until the study conclusion; B died within 28 days of SARS-CoV-2 infection so was not followed-up; C commenced follow-up from 28 days after SARS-CoV-2 infection until they were censored (i.e. for outcome event, death, or ESRD). **D-E: Examples of matched contemporary comparators.** D was matched to an individual with SARS-CoV-2 infection and followed-up from 28 days after matching until the study conclusion; E was matched to an individual with SARS-CoV-2 infection and followed-up from 28 days after matching until they were first recorded with SARS-CoV-2 infection themselves when they were censored from further follow-up as an unexposed comparator and then followed-up as an exposed case from 28 days after infection until the study conclusion. **F-G: Examples of matched historical comparators from 2018-2019.** F was matched to an individual with SARS-CoV-2 infection and followed-up from 28 days after matching until the study conclusion; G died within 28 days of matching so was not followed-up; H commenced follow-up from 28 days after matching until they were censored (i.e. for outcome event, death, or ESRD). **I-J: Examples of unmatched historical comparators hospitalised for pneumonia from 2018-2019.** I was followed-up from 28 days after admission for pneumonia until the study conclusion. J died within 28 days of admission for pneumonia so was not followed-up.

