## 4.5 Study measures

### 4.5.1 Exposure

We will identify recorded SARS-CoV-2 infection using data from SGSS, primary care records and SUS. We will include all codes indicative of SARS-CoV-2 infection. SGSS contains the date of an individual's earliest positive SARS-CoV-2 test results from Pillar 1

(NHS and Public Health England laboratories) and Pillar 2 (commercial partners) between 1 February 2020 to the most recent available time point (i.e. the COVID-19 pandemic era).

Individuals meet criteria for inclusion in the COVID-19 exposed group if they:

- Tested positive for SARS-CoV-2 infection in SGSS
- Had a primary care code indicative of SARS-CoV-2 infection
- Discharged from hospital with an International classification of Diseases Version 10 (ICD-10) code in SUS indicative of COVID-19

The index date for those exposed to COVID-19 will be from 28 days after first recording of SARS-CoV-2 infection (i.e., after the earliest date of the record of a positive test in SGSS, primary care coding, or admission in SUS).

Looking at all identified SARS-CoV-2 infections will allow us to investigate how many adverse kidney outcomes can be prevented by preventing SARS-CoV-2 infection altogether through comparisons with people from the general population without known infection. We will also be able to investigate whether outcomes vary based on infection severity (hospitalisation, critical illness, mechanical ventilation and AKI [including requiring RRT]) as well as calendar time and vaccination status through further stratification based on morbidity coding (ICD-10 codes) from SUS. We will categorise people as i) unvaccinated if they had not received any vaccine dose at least 7 days before first recording of SARS-CoV-2 infection, ii) single dose vaccinated if they had received one vaccine dose at least 7 days before first recording of SARS-CoV-2 infection, iii) double vaccinated if they had received two vaccine doses at least 7 days before first recording of SARS-CoV-2 infection, and iv) more than double vaccinated if they had received more than two vaccine doses (including booster doses) at least 7 days before first recording of SARS-CoV-2 infection.

Hospitalised COVID-19 cases will be further investigated through a separate comparison with a historical group. Additional levels of exposure for those hospitalised will include critical care admission, mechanical ventilation, acute KRT and AKI, determined from ICD-10 and procedural codes in SUS.

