| 
4.5.1 Exposure
                                                                | 
We will also be able to investigate whether outcomes vary based on infection severity (hospitalisation, critical illness, mechanical ventilation and acute kidney injury [including requiring renal replacement therapy]) as well as calendar time and vaccination status...
                                                                                                                                                                       | 
We did not use mechanical ventilation or renal replacement therapy as additional levels of exposure.
                                                                             | 
We decided there would be little added benefit in disaggregating mechanical ventilation from critical care admissions, especially in the context of heightened competing risk of death.
 
We did not include acute renal replacement therapy as an additional level of exposure as it was included in our outcome definition (we defined kidney failure as incident dialysis [including any acute renal replacement therapy records recorded between initial COVID-19 record and index date 28 days later on day 1 of follow up], kidney transplantation, or estimated glomerular filtration rate <15ml/min/1.73m^2). However, we investigated the effect of including and excluding acute renal replacement
 |

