|                               |                                                                                                                                                                                                                                                                                                                                                                                                                                                                                                                                                                                                                                                                           |                                                                                                                                                                                                                                                                                                                                                                                                                                                                                                                                                                                                                       | 
therapy (recorded in the 28 days after initial COVID-19 record) from our outcome definition through sensitivity analyses.
 
Instead of calendar time and vaccination status being investigated as additional levels of exposure, we fitted these as interaction terms in secondary analysis to be able to determine stratum-specific effects on individuals with and without COVID-19.
                                                                                                                                                 |

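### The kidney-failure definition in the deviations log counts acute renal replacement therapy from the 28 days before follow-up starts, and these records can dominate the main overall rate and hazard ratio

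*Protocol*

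**What the plan says.** **Time zero.** Protocol section 4.5.1 sets the index date of exposed people: it "will be from 28 days after first recording of SARS-CoV-2 infection". For contemporary comparators, section 4.4.4 says "we will follow all eligible individuals from the index date". The Figure 1 legend shows matched comparators "followed-up from 28 days after matching until the study conclusion". In every group, then, the 28 days before the index date carry no follow-up.

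**Planned use of those 28 days.** Section 4.4.4 gives the purpose of the gap: "we will be able to look back and further stratify the exposure by measures of SARS-CoV-2 severity". Acute KRT is one of those severity levels (objectives 1d and 2d).

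**What the log says was done.** The deviations table, row 4.5.1, drops acute renal replacement therapy (RRT) as an exposure level because it now belongs to the outcome. Kidney failure covers dialysis that is new, "including any acute renal replacement therapy records recorded between initial COVID-19 record and index date 28 days later on day 1 of follow up", plus transplantation or an eGFR below 15. The log adds that results with and without acute renal replacement "therapy (recorded in the 28 days after initial COVID-19 record) from our outcome definition through sensitivity analyses" were examined. The rows for sections 4.6.1 and 4.6.2 report Cox models stratified by matched set, overall and by period of follow-up.

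**The concern.** An event dated before time zero is moved to day 1. The numerator then covers 28 days that the denominator leaves out, and those are the days of the acute illness. Dialysis given in that window may be temporary. The protocol itself separates short-term dialysis for AKI (section 1.1) from ESRD, which it ties to long-term KRT (section 2.2). Section 4.6.4, item 4, treats AKI counted as ESRD as misclassification to be guarded against, but its restriction to dialysis or transplant codes would not remove acute dialysis.

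The window is anchored to the first COVID-19 record. The log states no matching window for general-population comparators (match date to index date) or for pneumonia comparators (admission to day 28).

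At stake are the overall kidney-failure rate and hazard ratio, above all for hospitalised people. A reader would take them as evidence about long-term kidney failure, when they may mostly reflect how often acute dialysis was given during the illness.

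**Working it through.** **Inputs**

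- N = 200,000 hospitalised survivors (section 5).
- p0 = 0.02% ESRD incidence in the general population (section 5). No time unit is given; it is taken here as annual, with one year of follow-up.
- HR after the index date: 1.0 (no effect), 1.6 (the detectable value in section 5) and 2.96 (the external cohort quoted there).
- a = share of 28-day survivors with acute RRT in the window. This is not given. Section 2.1 reports that "3% of over 80,000 inpatients required kidney replacement therapy (KRT"), but that covers all inpatients, including those who died. The range 0.1% to 1% is an assumption.

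**Step 1: reproduce the plan's figure.** A two-sided 5% test of two proportions with pooled variance, 5:1 matching, and event proportions 0.0002 × HR against 0.0002 gives 87.5% power at N = 200,000 and HR 1.6. Table 1 prints 88%. All 36 cells agree within 1.0 percentage point, so N and p0 are being read as the plan reads them.

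**Step 2: events after the index date** = N × p0 × HR.

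- HR 1.0: 200,000 × 0.0002 = 40
- HR 1.6: 64
- HR 2.96: 118.4

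**Step 3: break-even.** Day-1 events number N × a. They equal the later events when a = p0 × HR: 0.02%, 0.032% and 0.059% at the three hazard ratios. These are 0.7% to 2.0% of the 3% inpatient figure.

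**Step 4: apparent ratio** = (N × a + N × p0 × HR) / (N × p0).

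| a | Day-1 events | HR 1.0: ratio (day-1 share) | HR 1.6 | HR 2.96 |
|---|---|---|---|---|
| 0.1% | 200 | 240/40 = 6.0 (83%) | 264/40 = 6.6 (76%) | 318.4/40 = 8.0 (63%) |
| 1% | 2,000 | 2,040/40 = 51 (98%) | 2,064/40 = 51.6 (97%) | 2,118.4/40 = 53.0 (94%) |

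**Step 5: dependence on the baseline.** If p0 were ten times higher (0.2%, a stress test) with HR 1.0, a = 0.1% gives (400 + 200)/400 = 1.5 and a = 1% gives (400 + 2,000)/400 = 6. Two years at 0.02% per year give (80 + 200)/80 = 3.5 and (80 + 2,000)/80 = 26.

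**Step 6: the whole infected cohort.** Take 1,000,000 infected (the largest row of Table 1), 200,000 of them hospitalised, with no acute RRT outside hospital and HR 1.0. There are 200 later events. The ratio is (200 + 200)/200 = 2 at a = 0.1% and (2,000 + 200)/200 = 11 at a = 1%.

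**Step 7: would the same window in general-population comparators cure it?** It would add 200,000 × 0.0002 × 28/365 = 3.1 events to the 40. The ratios become 240/43.1 = 5.6 and 2,040/43.1 = 47.4, against 6 and 51. The distortion comes mainly from counting the acute phase, not from the unequal window. No figure in the protocol allows the same check for pneumonia comparators, where acute RRT during the admission is plausible and the asymmetry could matter more.

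**Step 8: the model.** Stratifying by matched set does not absorb this. A day-1 event in the exposed member occurs with essentially the whole set at risk. That person then leaves, and later comparator events in the set carry no information on the contrast.

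**The case against.** The strongest reply is that the practice is disclosed and tested. The sentence that defines the outcome goes on to say that versions with and without these records were examined, and period-specific hazard ratios confine day-1 events to the first period. This stands, and it narrows the point to which version carries the headline.

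There is also a rationale. Someone who starts dialysis in the window and never comes off it has kidney failure dating from the infection, and dropping the record could miss or misdate it. That is a reason to show both versions. It does not justify dating every such record to day 1 of long-term follow-up.

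Several stronger readings are tempting but not supported:

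- *The rule was applied to COVID-19 cases only.* That is the literal reading of a window anchored to the COVID-19 record. The log does not say how comparators were handled, and step 7 shows it hardly matters for the general-population groups.
- *The later course of acutely dialysed people is never observed.* The excluding version removes records from the outcome definition, not people from the cohort, so their later events may be counted there.
- *They leave the AKI and death analyses on day 1 and become day-1 events in the eGFR outcome.* This follows if section 4.4.5 ("In all analyses we will follow individuals until the earliest of: record of specific kidney outcome under investigation, ESRD, death") and the ESRD component in section 4.5.2.2 are joined to the new definition. The log does not report it.
- *The ratio is about 150.* Putting 3% into step 4 gives 6,040/40 = 151, but that applies a figure for all inpatients to 28-day survivors.

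**Conclusion.** The point holds. By the log's own definition, acute RRT from before time zero enters the primary kidney-failure outcome as a day-1 event, and the main overall rate and hazard ratio carry it. The firm part of the size is the break-even: about 0.02% to 0.06% of hospitalised survivors is enough for these records to match all later events. The apparent ratios of about 6 to 51 illustrate what an assumed 0.1% to 1% would do with no effect after the index date. They rest on 0.02% being annual, on one year of follow-up, and on comparators of hospitalised patients having the general-population rate; a higher baseline shrinks them. The documents support saying that acute-phase dialysis can dominate the headline estimate. Without event counts they do not show that it did.

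**What to change.** 1. Make the version without acute RRT from days 0 to 28 the main kidney-failure analysis, counting only records dated after the index date, in both groups.
2. Apply the same rule to the kidney-failure component of the eGFR outcome and to ESRD as an end of follow-up in the AKI and death analyses.
3. Report RRT in days 0 to 28 as a separate count.
4. Where acute RRT is kept as an outcome in a sensitivity analysis, start the clock at first recording, admission or match date in all groups, and count the same window in comparators.
5. Label the swap as a post hoc change and show both versions side by side.

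**Cost.** The log says the excluding version was run, so swapping main and sensitivity analyses is cheap. Items 2 and 4 may need rerunning, and the log mentions loss of data access after 30 June 2024; if a rerun is impossible, that should be stated as a limitation. There will be fewer primary events and wider intervals. Table 1 was built on the 0.02% incidence with no separate allowance for acute-phase dialysis. By the method of step 1, power at 200,000 exposed and HR 1.6 is 84% at the 3:1 matching used. Dialysis that begins in the window and continues past day 28 will still produce post-index records, so the report should say how such people are counted.
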